# Number of Participants

60 patients (120 eyes) will be enrolled in this study after an initial ad-hoc power calculation was performed to determine necessity to reach statistical significance.

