# Number of Participants

Following a preliminary data collection, we were able to estimate the sample size needed to reach statistically significant results. Assuming that the manual gonioscopy and automated gonioscopy GS-1 have an equal probability of recording a diagnosis, Cohen's Kappa of 0.34 was measured. To detect a fair agreement between the two modalities, while achieving 80% power and 5% type I error, we will need to collect data from 94 eyes. To account for the portion of images that are uninterpretable due to poor quality (10-20%), we asses a total of 120 eyes (60 participants) would be satisfactory for us to estimate the GS-1 as a diagnostic tool accurately.

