# Eligibility Criteria/Vulnerable Populations

Inclusion criteria:

-Aged 18 and older

-Diagnosed with glaucoma or glaucoma suspect Glaucoma Suspect

- - 1. Glaucomatous optic neuropathy as described in the glaucoma patients below
    2. AND/OR ocular hypertension (IOP > 21 mm Hg)
    3. Normal visual field Glaucoma Patients

1. Clinical characteristics of glaucoma: ONH abnormalities: global rim thinning, rim notch, or disc hemorrhage; RNFL defect

Typical glaucomatous field loss in reliable VF, reproducible glaucoma hemifield tests labeled outside normal limits on at least two consecutive tests.

-Both eyes will be included, except in cases where only one eye meets study criteria

Exclusion criteria:

-Corneal opacities (scars, edema, etc.)

-Pregnant or planning to become pregnant

-Inability to fixate gaze

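### Section 5.3 counts eyes and makes no allowance for two eyes per patient, so the stated 80% power is unsupported and the 5% type I error depends on how pairing is analysed

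*Protocol*

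**What the plan says.** Section 5.3 starts from preliminary data in which "Cohen's Kappa of 0.34 was measured", with the condition "Assuming that the manual gonioscopy and automated gonioscopy GS-1 have an equal probability of recording a diagnosis". The aim is put as "To detect a fair agreement between the two modalities", and the requirement follows: "while achieving 80% power and 5% type I error, we will need to collect data from 94 eyes". The only inflation is for images too poor to grade, put at 10-20%. The section then concludes that "we asses a total of 120 eyes (60 participants) would be satisfactory for us to estimate the GS-1 as a diagnostic tool accurately".

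The Synopsis repeats the total: "60 patients (120 eyes) will be enrolled in this study". Section 5.4 sets two eyes per patient as the default but allows for fewer: "Both eyes will be included, except in cases where only one eye meets study criteria".

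The protocol gives no inter-eye correlation, design effect or effective number of eyes. It also does not state the null kappa, the sidedness of the test, the number of grading categories or their prevalence. Section 4.2 names ANOVA, kappa and the intraclass correlation coefficient (ICC). Section 6.7 adds linear and quadratic models and unspecified further methods. Neither section says how fellow eyes are handled.

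**The concern.** Fellow eyes of one patient tend to have similar angles, so a second eye usually adds less information than a second patient. A requirement counted in eyes, and filled with two eyes per patient, holds only if fellow eyes are close to independent or if the figure has been inflated for their correlation. Section 5.3 neither argues the first nor does the second.

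At stake are the two operating characteristics the section claims. Power may be below 80%. The precision reported for agreement between the GS-1 and conventional gonioscopy would also be overstated if eyes were analysed as independent. A later analysis plan can correct the analysis, but it cannot put into the sample size an allowance that was never made. A correct clustered analysis would simply show the lower power.

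**Working it through.** **Inputs from the protocol.** 94 evaluable eyes; 80% power; 5% type I error (taken as two-sided); preliminary kappa 0.34; 10-20% image loss; 120 eyes from 60 patients.

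**Assumed, because not stated.** The inter-eye correlation of grades, and hence the design effect DE. For two eyes per patient and kappa near 0, DE is about 1 + ρ₁ρ₂, where ρ₁ and ρ₂ are the inter-eye correlations under the two methods. Correlations of 0.6 to 0.9 in both give 1 + 0.36 = 1.36 up to 1 + 0.81, about 1.8.

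**1. The plan's own steps.** 94/0.9 = 104.4, so 105 eyes; 94/0.8 = 117.5, so 118, rounded to 120. This step reproduces. Evaluable eyes would be 120 × 0.8 = 96 or 120 × 0.9 = 108.

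The 94 itself does not reproduce. For kappa 0.34 against 0 with two categories at prevalence 0.5, the large-sample variance term is 1 under the null and 1 − 0.34² = 0.8844 under the alternative, so

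n = [(1.96 + 0.8416 × √0.8844)/0.34]² = (2.7515/0.34)² ≈ 65.5, or 66 eyes.

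A goodness-of-fit version gives 67.9, or 68 eyes. Values near 94 appear only with unstated inputs, for example a null kappa of 0.05 (90-96 eyes, depending on method and prevalence).

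**2. Break-even, taking 94 independent eyes = 80% as given.** Power stays at 80% while evaluable eyes/DE is at least 94. The limits are 96/94 = 1.02 at 20% loss and 108/94 = 1.15 at 10% loss.

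**3. Power of 94 eyes under the assumed design effects.**
- Reading A (94 = 80%): Φ(2.80/√DE − 1.96), where 2.80 = 1.96 + 0.84.
- Reading B (kappa 0.34 against 0, two categories, 50/50): Φ[(0.34 × √(94/DE) − 1.96)/√0.8844].

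| DE | Effective eyes, 94/DE | Reading A | Reading B |
|---|---|---|---|
| 1 | 94 | 80% | 92% |
| 1.36 | 69 | 67% | 82% |
| 1.5 | 63 | 63% | 78% |
| 1.8 | 52 | 55% | 70% |

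Under reading B, 96 evaluable eyes keep 80% power up to DE of about 96/67.9 = 1.41 to 96/65.5 = 1.47.

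**4. Type I error of a kappa test that ignores pairing.** The approximate rate is 2[1 − Φ(1.96/√(1 + φ²))], with inter-eye φ equal in both methods. A null simulation with 48 patients × 2 eyes = 96 eyes, 20,000 runs per setting, agrees with it.

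| Inter-eye φ | Formula | Simulation |
|---|---|---|
| 0 | 5.0% | 5.0% |
| 0.41 | 7.0% | 7.1% |
| 0.59 | 9.1% | 9.4% |
| 0.71 | 11.0% | 11.1% |
| 0.80 | 12.6% | 12.9% |

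**5. One-eye participants.** Sixty patients yield 120 eyes only if all contribute both. With three one-eye participants, 117 × 0.8 = 93.6, just under 94. At 10% loss 105 eyes suffice, so 15 one-eye participants could be absorbed.

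**The case against.** A reader might infer from the missing allowance that 80% power is not delivered. The documents do not support that. The size of any loss depends on a correlation they do not give. The 94 that anchors reading A cannot be rebuilt from the stated inputs, and the plainest reading of them needs only 66-68 eyes, which leaves slack for moderate correlation. This objection stands and limits the conclusion on power. It does not rescue section 5.3, which says 94 eyes are needed and cannot rely on slack it does not declare.

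A reader might also infer that the 5% type I error is already broken, or that standard errors for kappa, the ICC and the ANOVA will all be too small. Type I error depends on the analysis. The protocol neither says that fellow eyes are treated as independent nor excludes it, and clustered variances are commonly left to an analysis plan, which is not at hand. For the ANOVA, the methods are compared on the same eyes, so what matters is the inter-eye correlation of between-method differences. An analysis that ignored same-eye pairing could even be conservative. Only kappa has been quantified here, so nothing is claimed about the size of any ANOVA or ICC effect.

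Two smaller objections also stand. The formula 1 + ρ₁ρ₂ is derived near kappa 0 and is only a guide under the alternative. The one-eye shortfall is negligible as quantified: 93.6 against 94 eyes moves power from 80% to about 79.8%.

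**Conclusion.** The calculation makes no stated allowance for two eyes per patient, and its image-loss margin leaves none. On the protocol's own requirement of 94 eyes, a design effect above about 1.02 (96 evaluable eyes) or 1.15 (108) takes power below 80%. With assumed design effects of 1.36 to 1.8, 94 eyes give about 67% to 55% on that figure, or about 82% to 70% if the test was kappa 0.34 against 0. The stated 80% is therefore unsupported rather than proven lost. The 5% type I error for kappa is conditional: it holds if the analysis accounts for pairing, and would be about 7-13% at inter-eye φ of 0.41-0.80 if it does not. These sizes rest on assumed correlations and a two-sided test. The one-eye participants are an inconsistency to tidy up, not a material loss of power.

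**What to change.** Keep 60 participants and change the wording.

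- State that the patient is the independent unit.
- For kappa and the ICC, use a patient-level cluster bootstrap or a cluster-adjusted variance. In the models, include a patient random effect with eye nested within patient, since each eye is measured by several methods.
- Restate section 5.3 with the null kappa, sidedness, number and prevalence of categories, an assumed range of inter-eye correlation, the resulting effective number of eyes, and the expected number of one-eye participants. Give the resulting power or confidence-interval width in place of 80%, and align the Synopsis.

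The cost is protocol and analysis-plan text and a less favourable stated power; no extra patients are needed. This discloses the limitation and does not remove it. Holding 80% on the protocol's own 94 at DE 1.5, for example, would take 94 × 1.5 = 141 evaluable eyes, 141/0.8 = 176.25 or 177 enrolled eyes, and so 89 patients. Reporting the precision that 60 patients can give is the proportionate choice for a single-visit agreement study.

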# Eligibility Criteria/Vulnerable Populations

Inclusion criteria:

-Aged 18 and older

-Diagnosed with glaucoma or glaucoma suspect Glaucoma Suspect

- - 1. Glaucomatous optic neuropathy as described in the glaucoma patients below
    2. AND/OR ocular hypertension (IOP > 21 mm Hg)
    3. Normal visual field Glaucoma Patients

1. Clinical characteristics of glaucoma: ONH abnormalities: global rim thinning, rim notch, or disc hemorrhage; RNFL defect

Typical glaucomatous field loss in reliable VF, reproducible glaucoma hemifield tests labeled outside normal limits on at least two consecutive tests.

-Both eyes will be included, except in cases where only one eye meets study criteria

Exclusion criteria:

-Corneal opacities (scars, edema, etc.)

-Pregnant or planning to become pregnant

-Inability to fixate gaze

# - Methods

# Study Procedure

Subjects who meet eligibility criteria will be identified by study team and will be consented for the study. During their usual ophthalmology visit, all subjects will undergo conventional gonioscopy, ultrasound biomicroscopy, and gonioscopy with NIDEK Gonioscope GS-1. The NIDEK Gonioscope GS-1 will only be used on patients who are in the study. The experimental part of the visit using the NIDEK Gonioscope GS-1 should take approximately 10 minutes,

For conventional gonioscopy, the clinician may obtain digital images of the iridocorneal angle using a slit lamp and goniolens. For ultrasound biomicroscopy, the clinician may obtain ultrasound images that will then be stored within the biomicroscope device. For gonioscopy with NIDEK Gonioscope GS-1, the device may obtain and store images of the iridocorneal angle.

Following collection of the images, one ophthalmologist may examine images obtained from conventional gonioscopy and determine the width of the iridocorneal angle. The same ophthalmologist will determine the width of the iridocorneal angle from the ultrasound biomicroscopy images. This ophthalmologist will be masked to patient names and diagnoses. A second and potentially third ophthalmologists may examine images obtained from NIDEK Gonioscope GS-1 and determine the width of the iridocorneal angle. These ophthalmologists will also be masked to patient names and diagnoses.

Statistical analysis will be performed to determine the association between the findings of iridocorneal angle width in conventional gonioscopy images, ultrasound biomicroscopy images, and NIDEK Gonioscope GS-1 images of each patient. Further statistical analysis will be performed to determine the inter-observer repeatability of the findings of the two ophthalmologists who examined the images from NIDEK Gonioscope GS-1.

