# Study Design

This is a prospective, non-randomized, cross-sectional, experimental study.

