# - Background

Gonioscopy is a vital part of the ophthalmologic examination, as it allows clinicians to evaluate the iridocorneal angle of the eye. The iridocorneal angle contains the orifice to the draining pathway of the aqueous humor from the anterior chamber into the canal of Schlemm. More acute, or “narrow,” angles can put patients at risk for glaucoma due to obstruction of the route of the fluid into the trabecular meshwork. Accumulation of pigment or inflammatory cells can also lead to obstructions of the drainage system and consequent increase in intraocular pressure. Gonioscopy allows clinicians to assess the width of the angle as well as look for any structural deformation or accumulation of material.

The goniolens is a specially designed lens to allow visualization of the angle that is placed on the patient’s cornea by the clinician during the ocular examination. When used in conjunction with a slit lamp, it gives the clinician a view of the iridocorneal angle, which is otherwise masked by the ocular configuration. Although it is considered the gold standard for assessment of the iridocorneal angle, gonioscopy can be difficult to perform. [1] The evaluation of the width of the iridocorneal angle is subjective and requires clinical experience. [1] As such, there is some inter-operator variability in the results obtained using this method.

Due to the time and skill required to obtain an accurate gonioscopic image on a conventional slit lamp, there has been interest in developing alternative methods to obtain quick, accurate, and reliable images of the iridocorneal angle. These alternative methods have involved the use of both new and existing technologies. For instance, currently available 3D Corneal and Anterior Segment Optical Coherence Tomography (3D CAS-OCT) has been used for this purpose. A study investigating the utility of 3D CAS-OCT in evaluating anterior segment parameters found a high degree of intra-grader repeatability, inter-grader repeatability, and correlation with conventional gonioscopy. [2]

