# Potential Risks

Because the multi-mirror prism touches the surface of the eye it carries a risk of infection. We will perform high level disinfection or low temperature sterilization (EOG sterilization) after any use of the prism to reduce this risk. Additionally, all exposed surfaces near the eye, as well as the chin rest and forehead rest of the instrument, will be cleaned with alcohol before participants are examined. The multi-mirror prism is made from cycloolefin polymer (COP) resin. *In vitro* cytotoxicity assays found that concentrations of up to 100% COP did not obstruct colony formation of V79 Chinese hamster lung cells. Ocular irritation tests showed that COP does not irritate the cornea, iris, or conjunctiva of rabbits.

The prism may cause a foreign body sensation to the patient during the capture of iridocorneal angle image which may cause some discomfort.

Ultrasound biomicroscopy is an FDA-approved technology that uses an ultrasound probe to visualize intraocular structures, including the iridocorneal angle. The ultrasound probe does not directly contact the eye, but rather a balloon filled with water is put in contact with the eye. The probe contacts the water balloon. There is risk of some minor patient discomfort during ultrasound biomicroscopy.

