# Primary Outcome Variables

Images obtained by the NIDEK Gonioscope GS-1 will be compared with ultrasound biomicroscopy images and digital gonioscopic images obtained using a goniolens and slit lamp to determine if the NIDEK Gonioscope GS-1 can accurately and reliably capture relevant findings. To determine the accuracy of the NIDEK Gonioscope GS-1, we will use ANOVA to determine if the iridocorneal angle measurements obtained from the NIDEK Gonioscope GS-1 are statistically similar to measurements obtained from ultrasound biomicroscopy and standard gonioscopy. To determine inter-observer reproducibility when using this device, two observers will examine each image obtained from NIDEK Gonioscope GS-1 and separately determine the iridocorneal angle. Inter-observer reproducibility will be determined using Kappa's statistics and intraclass correlation coefficient. Lastly, we will determine if the time it takes to obtain images from the NIDEK Gonioscope GS-1 is statistically different from the time it takes to obtain images by conventional gonioscopy. This will be done via ANOVA.

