# Device Specifications

The NIDEK Gonioscope GS-1 obtains gonioscopic images without using a goniolens or slit lamp. This device captures 360° images of the anterior segment, including the iridocorneal angle, in a single examination. The 16-face multi-mirror prism projects light onto the patient's iridocorneal angle and its peripheral area, and uses an image sensor to generate the image. A coupled gel will be applied to the prism tip prior to using the device. This gel reduces the refraction angle between the patient's cornea and the prism and moderates the variation in each patient's corneal shape.

Although the NIDEK Gonioscope GS-1 is not currently an FDA-approved device, it is a non- significant risk device under the criteria of 21 CFR 812.3 (m):

- - 1. It is NOT intented as an implant and does NOT present a potential for serious risk to the health, safety, or welfare of a subject
    2. It is NOT purported or represented to be for a use in supporting or sustaining human life and does NOT present a potential for serious risk to the health, safety, or welfare of a subject
    3. It is for a use of substantial importance in diagnosing, curing, mitigating, or treating disease, or otherwise preventing impairment of human health and does NOT present a potential for serious risk to the health, safety, or welfare of a subject

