# Informed Consent

The study will take place during the course of a single visit. Subjects will be approached by a study team member during a routine clinical visit and will be asked to participate. They will be given ample time to read, understand, and provide informed consent.

Documentation of the informed consent process will be used to ensure that the appropriate questions have been asked to the prospective participant.

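### The order of goniolens and GS-1 imaging within the visit is neither controlled nor recorded, so an order effect could pass for a device difference in acquisition time

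*Protocol*

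**What the plan says.** Under Methods, Study Procedure, the protocol has every participant examined by all three methods: "all subjects will undergo conventional gonioscopy, ultrasound biomicroscopy, and gonioscopy with NIDEK Gonioscope GS-1". Informed Consent confines this to one occasion: "The study will take place during the course of a single visit".

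Each method involves contact with the eye. Background describes the goniolens as placed on the patient's "cornea by the clinician during the ocular examination". Potential Risks says of the GS-1 "Because the multi-mirror prism touches the surface of the eye it carries a risk of infection", and of ultrasound biomicroscopy that "a balloon filled with water is put in contact with the eye". The same section expects possible discomfort from the GS-1 prism and from ultrasound.

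Primary Outcome Variables includes acquisition time: "we will determine if the time it takes to obtain images from the NIDEK Gonioscope GS-1 is statistically different" from that of conventional gonioscopy, by ANOVA. Ultrasound has no part in the time comparison. The angle comparison, in the same section, covers all three methods.

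The protocol does not say which procedure comes first, how the order is chosen, what interval separates the procedures, or that the order is to be written down. Neither Primary Outcome Variables nor Primary Analyses names order or period as a factor.

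**The concern.** When each participant is measured by both devices, the participant serves as his or her own control and differences between patients drop out of the comparison. Differences between the first and the second examination do not. A patient may cooperate less, or more, by the second procedure; the eye may be uncomfortable or watering after earlier contact. Any of these can lengthen or shorten the time to a usable image.

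If one device always comes second, the paired difference estimates the device effect plus the order effect, and no analysis can separate the two. The time result would then be open to a simple alternative explanation. It bears on the protocol's stated hope, in Background, that the GS-1 could speed up examination in glaucoma clinics.

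The sequence is a matter of study conduct. A SAP written later can add an order term only if the order was recorded and varied; it cannot restore balance.

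**Working it through.** **Inputs from the protocol.** 60 participants (Number of Participants); all three procedures in each of them (Study Procedure); one visit (Informed Consent); a test of the time difference between GS-1 and conventional gonioscopy (Primary Outcome Variables). The 5% type I error is taken from the sample-size paragraph, which concerns kappa rather than time. There is no protocol figure for an order effect, so there is none to reproduce.

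**Assumptions.** One time per device per participant, giving 60 paired differences; a two-sided 5% paired t-test, which is what a within-participant ANOVA of two devices amounts to; no true device difference; an order effect that shifts the mean paired difference by g standard deviations (of that difference) when the same device is always first.

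**Step 1: is the order fixed by the text?** It is not. Study Procedure and Primary Analyses list conventional gonioscopy, ultrasound, GS-1. The Primary Objective in the Synopsis names GS-1, then conventional gonioscopy, then ultrasound. Under Study Objectives, both the Primary Objective and the Primary Outcome Variables put ultrasound before conventional gonioscopy. The lists are not sequences. Recruitment, Enrollment and Retention says eligibility follows from an eye examination, but not whether that examination includes the study gonioscopy.

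**Step 2: one habitual order.** The test statistic follows a noncentral t distribution with 59 degrees of freedom and noncentrality g × √60. The critical value is 2.001. The probability of declaring a difference is P(|T| > 2.001):

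| Assumed g | g × √60 | Probability of declaring a device difference |
|---|---|---|
| 0 | 0 | 5% |
| 0.1 | 0.77 | 12% |
| 0.2 | 1.55 | 33% |
| 0.3 | 2.32 | 63% |
| 0.4 | 3.10 | 86% |

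A normal approximation gives 12%, 34% and 64% at g = 0.1, 0.2 and 0.3, so the result does not depend on the choice of method.

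**Step 3: mixed order.** If a share f of participants has one given device first, the remaining bias is (2f − 1) × g:

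- f = 1 (always the same order): the full g
- f = 0.75: 0.5 × g
- f = 0.5 (balanced): 0

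At a 75:25 split, an assumed g of 0.2 leaves a bias of 0.1, which by the table in Step 2 corresponds to about 12%. This holds the standard deviation fixed.

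**Step 4: why an order term as well as balance.** With a balanced order and no order term, the bias is gone, but the order effect adds to the spread of the differences: the variance is multiplied by 1 + g², for example 1 + 0.4² = 1.16 at g = 0.4. An order term removes that extra variance.

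**The case against.** Much of the case against a stronger version stands.

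- **GS-1 always last.** A reader might infer this because Study Procedure names it last and calls it the experimental part of the visit. The protocol states no sequence, and its own lists differ. Complete confounding is therefore conditional on a habitual order that no section prescribes.
- **The design label.** A reader might take "This is a prospective, non-randomized, cross-sectional, experimental study" as a decision not to randomise the order. It may equally refer to allocating patients to groups. The point rests on the absence of any order rule, not on that label.
- **Gel carry-over.** Device Specifications says "A coupled gel will be applied to the prism tip prior to using the device", which might suggest residue in later images. If GS-1 came last in an eye, its gel could not affect another image of that eye. The documents also do not support the idea that carry-over would fall on one device only.
- **Accuracy equally at risk.** Angle width is read afterwards from stored images, by readers masked to names and diagnoses. An order effect would have to act through the eye or image quality. The protocol expects 10-20% of images to be uninterpretable but does not link this to order. The route is possible and not shown.
- **The percentages.** They follow from assumed shifts; any unmodelled bias of that size would give the same figures. They also presume no true time difference. If there is one, the issue is bias in its estimate.

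It can also be said that this is an omission and that no statement in the protocol is wrong. That is fair as to severity. It does not remove the point, because an order left unrecorded during the study cannot be recovered at analysis.

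**Conclusion.** The point holds for the time comparison between GS-1 and conventional gonioscopy. The order of the two examinations is left open, so an order effect is fully confounded with device under one habitual order and partly confounded under a haphazard mix. For the angle comparison there is only a possible indirect effect, which the documents do not demonstrate.

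The size is unknown. The range of 12% to 86% false declarations applies to assumed shifts of 0.1 to 0.4 SD, a constant order, 60 independent paired times and no true difference. It shows how sensitive the test would be and does not estimate what will happen. Timing each eye separately would give up to 120 differences, but two eyes of one patient are not independent, so the figures do not carry over directly.

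This is an inexpensive improvement, of low severity. It does not undermine the study as a whole.

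**What to change.** In Study Procedure, add that each participant is assigned, by alternation or a short random list, to have either goniolens imaging or GS-1 imaging first, and that the actual order of all three procedures is recorded. In the time analysis, include a term for order. Balance removes an additive order effect; it would not fully remove carry-over that differs between the devices. Ultrasound may keep a fixed place if clinic flow needs it, since it is not part of the time comparison, but its position relative to GS-1 would then remain uncontrolled for the angle comparison.

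The cost is an allocation list, one data field and some change to clinic flow for about half of the participants.

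If the usual visit requires conventional gonioscopy first, the protocol should state that order, record it, and say that the time result compares the devices in that sequence and cannot separate device from position.

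### Both GS-1 angle-width comparisons are fully confounded with the reader, because no ophthalmologist is assigned to grade both GS-1 and a reference modality

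*Protocol*

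**What the plan says.** The reading plan is in the Protocol, Methods, Study Procedure.

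- Conventional gonioscopy: "one ophthalmologist may examine images obtained from conventional gonioscopy and determine the width of the iridocorneal angle".
- UBM: "The same ophthalmologist will determine the width of the iridocorneal angle from the ultrasound biomicroscopy images".
- GS-1: "A second and potentially third ophthalmologists may examine images obtained from NIDEK Gonioscope GS-1 and determine the width of the iridocorneal angle".
- Masking of the reader of the two references: "This ophthalmologist will be masked to patient names and diagnoses". The GS-1 readers are masked in the same way.

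Under Primary Outcome Variables, accuracy is to be judged by an ANOVA of whether the GS-1 measurements "are statistically similar to measurements obtained from ultrasound biomicroscopy and standard gonioscopy". Inter-observer reproducibility is a separate item, for which "two observers will examine each image obtained from NIDEK Gonioscope GS-1 and separately determine the iridocorneal angle". Study Procedure and Primary Analyses also relate the three modalities to each other.

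On whether readers differ, the Background section states that "there is some inter-operator variability in the results obtained using this method" and calls the evaluation of angle width subjective. The Problem Statement describes repeatability and reliability with a conventional goniolens as user-dependent.

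**The concern.** The primary objective asks how GS-1 compares with gonioscopy and UBM. Under the stated allocation, whenever the modality changes from a reference to GS-1, the person grading changes too. An observed difference could come from the device, from one ophthalmologist habitually grading wider or narrower than another, or from both. An offset in the opposite direction could equally hide a real device difference. The study's own rationale is that graders differ, so a zero reader effect cannot simply be assumed.

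This is not a detail that an analysis plan could settle. The readings needed to separate the two effects are not among those the protocol assigns.

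**Working it through.** **Step 1: which cells are filled.** Inputs are from Study Procedure, with the two GS-1 observers of Primary Outcome Variables taken as readers 2 and 3.

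| Modality | Reader 1 | Reader 2 | Reader 3 |
|---|---|---|---|
| Gonioscopy (G) | yes | – | – |
| UBM (U) | yes | – | – |
| GS-1 (S) | – | yes | yes |

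**Step 2: what can be estimated.** Take the simplest model: expected grade = μ + modality effect α + reader effect β.

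- S (reader 2) − G (reader 1) = (α_S − α_G) + (β_2 − β_1)
- S (reader 2) − U (reader 1) = (α_S − α_U) + (β_2 − β_1)
- U (reader 1) − G (reader 1) = α_U − α_G
- S (reader 3) − S (reader 2) = β_3 − β_2

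No cell supplies β_2 − β_1 on its own. The model has 5 free parameters (intercept, two modality contrasts, two reader contrasts), and the design matrix has rank 4. GS-1 minus gonioscopy and GS-1 minus UBM are not estimable; UBM minus gonioscopy is. A second GS-1 reader shows the spread among GS-1 readers but not their offset from reader 1.

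**Step 3: add one cell, GS-1 graded by reader 1.** Then S (reader 1) − G (reader 1) = α_S − α_G, and likewise for UBM. The rank becomes 5 of 5 and both contrasts are estimable.

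**Step 4: possible size.** The protocol gives no reader offset, so there is no planned figure to reproduce and everything in this step is an assumption. True angle width is N(2, SD 1.1) on a grade scale, and each reading is rounded and limited to 0–4. The two devices are identical. Each reading has independent noise of SD 0.3, and the GS-1 reader adds a constant offset.

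| Reader offset (grades) | Unweighted kappa, GS-1 vs reference | Spurious mean difference (grades) |
|---|---|---|
| 0 | 0.59 | 0 |
| 0.1 | 0.57 | 0.09 |
| 0.25 | 0.52 | 0.23 |
| 0.5 | 0.36 | 0.46 |
| 0.75 | 0.18 | 0.68 |

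With one reader on both modalities, kappa stays at 0.59.

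A second set of assumptions (eye SD 1.2, noise SD 0.4, identical devices) gives kappa of 0.49, 0.46, 0.36 and 0.23 at offsets of 0, 0.25, 0.5 and 0.75. With 94 eyes, treated as independent, a paired t test at 5% declares the identical devices different in 4%, 89%, 100% and 100% of runs. A quarter-grade offset thus barely moves kappa but can decide a test of mean difference.

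**Step 5: number of readings.** Planned: 120 gonioscopy + 120 UBM + 2 × 120 GS-1 = 480. With reader 1 also on GS-1: 480 + 120 = 600. Full crossing: 3 readers × 3 modalities × 120 = 1,080, which is 600 more than planned.

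**The case against.** Separate readers have a legitimate purpose: a GS-1 grader who has never seen the reference images cannot be influenced by them. That benefit is real, but separate masked sessions with coded images serve the same purpose without tying reader to device.

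The reading plan is also loosely worded, with readers who may examine images and a third reader who is only potential. That wording does not exclude a crossed reading, but nothing in the protocol provides for one.

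The problem is not irreversible. The protocol says that GS-1 images can be stored, so a later masked re-reading by reader 1 is possible without recalling patients. This stands. The limitation belongs to the planned readings, not to the images.

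A reader might infer three stronger conclusions that the protocol does not support:

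- *Every device comparison is confounded.* Gonioscopy and UBM share a reader, acquisition time involves no grading, and agreement between the GS-1 observers stays within one modality.
- *Reader differences explain the pilot kappa of 0.34.* Number of Participants ties that kappa to recording a diagnosis and states neither its scale nor who read the images. In the first model of Step 4, a kappa on grades split into two categories is 0.61 to 0.63 at an offset of 0.5 grade (0.63 to 0.65 without reading noise). No inference about 0.34 is warranted.
- *Reader 1 sees the other modality's grade and pulls the two references together.* The protocol is silent on this. It masks names and diagnoses and de-identifies the data, which may already make linking harder. Masking to the other grade is not stated, and no more than that can be said.

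**Conclusion.** The concern holds for both GS-1 angle-width comparisons, against gonioscopy and against UBM. Under the stated allocation each estimates device difference plus reader difference, and the two cannot be separated from the planned readings. This follows from the allocation alone and needs no numerical assumption.

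How much it matters depends on the reader offset, which the protocol does not give. Over an assumed range of 0 to 0.75 grade, the effect runs from none to a kappa of about 0.18 instead of 0.59 and a spurious mean difference of 0.68 grade. Those figures assume five grades, an unweighted kappa, a constant offset, and the eye and noise SDs given above; they illustrate and do not predict. Since the affected comparisons are the primary objective and the remedy is cheap, the allocation should be changed before the images are read.

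**What to change.** Amend Study Procedure so that the ophthalmologist who grades gonioscopy and UBM also grades the stored, coded GS-1 images. This should be done in a separate session, in random order, masked to eye identity and to the grades from the other modalities. State in the same amendment that this reader is masked to the other modality's grade when reading gonioscopy and UBM, and make storage of the GS-1 images definite rather than optional. Make the within-reader comparison of GS-1 with each reference primary, with reader as a factor in the model. Keep the other GS-1 readers for inter-observer agreement.

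The cost is about 120 extra eye-readings by an existing reader and a small amendment, with no new staff and no added patient procedure. With this minimum change, the direct within-reader comparison rests on one ophthalmologist. Crossing three readers with all three modalities would show whether it carries over to others, at about 600 extra readings. It would also need gonioscopy images to be stored for every eye, whereas Study Procedure makes obtaining them optional. That larger version is desirable but optional.
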